**Footnotes for schedule of events:**

\*In case of cross-over                      #measured until hospital discharge                      †Once between day 35 and day 84  
( ) Follow-up by regular phone calls                      ‡Blood collection before CP administration

1. **Observation time** for all patients is expected to be at least 3 months after entry into the study. Patients receive convalescent plasma for two days (day 1 and day 2) or standard of care. For patients in the standard arm, cross over is allowed from day 10 in case of not improving or worsening clinical condition. There is a regular *follow-up* of 3 months. All discharged patients are followed by regular phone calls (scheduled days: 14, 17, 21, 24, 28, 32, 42, 49, 56, 70, 84). In person visits after discharge are only advised if clinically indicated. Timing of all visits must be based on the date of first CP administration. The study period ends on the day of the last follow-up visit of the last randomized patient. All Patients with ongoing plasma-related toxicities must be followed until all plasma-related toxicities are resolved.
2. **Informed consent and patient registration:** every patient must sign the informed consent to participate in this trial before starting any trial-related procedures. After signature, a patient ID (three-digit) is generated via registration in the eCRF system. After completion of the screening/baseline visit and assessment of the inclusion and exclusion criteria, **randomisation** is carried out by the responsible investigator **online via <https://randomizer.at>** (Uni Graz) with assignment of the random number.
3. **Demographics:** gender, year of birth, ethnicity
4. **Medical history:** date and type of first symptoms and detailed information on pretreatment including type and composition of prior therapy, family history (cancer, cardiovascular disease, diabetes, rheumatological disease), additional medical history on concomitant diseases in particular cancer and autoimmune diseases and their treatment.
5. **Information on smoking;** duration and amount, pack-years
6. **Signs/symptoms:** infection related and unrelated signs and symptoms, in particular cough, myalgia, fatigue, diarrhoea, vomiting,

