7. **Vital signs:** WHO performance status, temperature (in grade centigrade), blood pressure/pulse, respiratory rate, at baseline: height (in cm), weight (in kg). After hospital discharge the patients are contacted by phone or e-mail and asked about their performance status until 84 days after randomization.
8. **Physical examination:** inspection, lung, cardiac and abdominal auscultation and percussion, palpation of the abdomen and lymph node sites, neurological examination
9. **Seven point ordinal scale:** Assessment of the seven point ordinal scale (1, not hospitalized with resumption of normal activities; 2, not hospitalized, but unable to resume normal activities; 3, hospitalized, not requiring supplemental oxygen; 4, hospitalized, requiring supplemental oxygen; 5, hospitalized, requiring nasal high-flow oxygen therapy, noninvasive mechanical ventilation, or both; 6, hospitalized, requiring ECMO, invasive mechanical ventilation, or both; and 7, death.
10. **SOFA-Score:** The sequential organ failure assessment score (SOFA score) is assessed to determine the extent of a person's organ function or rate of failure. It integrates scoring of the respiratory system, nervous system, cardiovascular system, liver, coagulation and kidneys (Appendix).
11. **Oxygen saturation (SaO2)** while breathing ambient air measured by pulse oximetry. See 7.3.2 for details.
12. Amount of oxygen supplementation: i) supplemental oxygen l/min; nasal high-flow oxygen therapy l/min noninvasive mechanical ventilation, ECMO, invasive ventilation
13. **Cross-over Assessment:** For cross-over, all inclusion / exclusion criteria (except mechanical ventilation/ECMO) must again be met as specified in Chapters 5.3 and 5.4. After Cross over, the visit schedule is restarted at day 1 in the experimental arm. The timing of subsequent visits is based on the day of first CP administration.
14. **ECHO:** at baseline and thereafter at investigator's discretion

15. **ECG:** 12-lead ECG, at baseline, and thereafter at investigator's discretion
16. **Hematology (local lab):** hemoglobin, RBC, PLT, WBC, Differential cell counts at baseline.

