### **6.6 Enrolment, Randomisation, Treatment Assignment**

A subject is considered enrolled when he or she has signed the Informed Consent form. The patient receives a screening number at the clinical site (number of site plus number of patient in ascending order, e. g. 001-001 for the first enrolled patient at site 01) via registration in the eCRF system (www.xxx.). The screening number is used to identify the

---

 This section of the study protocol is defined as reference safety information (RSI).

subject throughout the clinical study and must be used on all study documentation related to the subject.

Clinical sites must complete the baseline case report forms for all enrolled subjects, even if the subject is not randomised or treated in this study.

Upon confirmation of eligibility (patients must meet all inclusion criteria and must not meet exclusion criteria), the clinical site must contact a centralized internet randomization system (<https://randomizer.at/>). Patients are randomized using block randomisation to one of the two arms, experimental arm or standard arm, in a 1:1 ratio considering a stratification according to the 4 risk groups (as described in the inclusion criteria).

All subjects randomised receive a unique randomisation number. All patients in the experimental group have to start CP treatment within 7 days of randomization. Patients withdrawn from the trial retain their Patient ID and randomization number.

The study is open-label.

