## **8 Ancillary and Post Trial Care**

Study ends for individual patients on day 84 (experimental arm and standard arm without cross over), day 94 (standard arm in case of cross over), or death. A telephone survey of patients (if applicable) or treating physician is conducted weekly after hospital discharge before day 84 (experimental arm and standard arm without cross over) or day 94 (standard arm in case of cross over).

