## **10.2 Analysis Variables**

### **10.2.1 Primary endpoint and primary estimand**

The main purpose of the study is to assess the time from randomization until an improvement within 84 days defined as two points on a seven point ordinal scale or live

discharge from the hospital in high-risk patients (group 1 to group 4) with SARS-CoV-2 infection requiring hospital admission by infusion of plasma from subjects after convalescence of a SARS-CoV-2 infection or standard of care. .

In the Addendum to the ICH E9 guideline (final version), the estimands framework is recommended as clear and transparent definition of “what is to be estimated” (International Council for Harmonization 2019). An estimand is defined through the treatment, the targeted population, the variable, a specification of how to handle intercurrent events (postrandomization events) and a population-level summary. In the following, the primary estimand corresponding to the primary objective is described.

The primary estimand corresponding the primary objective is defined as follows:

**Treatment:** Infusion of frozen CP (on two days of intervention from two different donors) vs. standard of care (as described in 5.7).

**Population:** The targeted population is defined through the in- and exclusion criteria.

**Variable:** Time from randomisation to clinical improvement within 84 days by two points on a seven point ordinal scale or live discharge from the hospital.

**Post-randomisation events:** live discharge from the hospital is incorporated into the variable definition (composite strategy), death from any cause within 84 days after randomization without previous improvement is taken into account by censoring deceased patients at day 84 (see sections 10.3 and 10.5.4 for rationale) ); treatment switch will be ignored (treatment policy strategy, see sections 10.3 and 10.5.4 for rationale); event-free patients at the end of the follow-up period are censored and drop-outs are censored at the last observation (hypothetical strategy).

**Summary measure:** Hypothesis testing is conducted using a log-rank test. The summary measure for effect quantification is the hazard ratio for the endpoint “clinical improvement by two points or live discharge” between the two treatment arms (which is estimated using Cox regression).

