### **10.5.4 Analysis of the Primary Endpoint**

The primary analysis will assess the null hypothesis “the cumulative improvement curves for the primary endpoint in the experimental and control arm are equal”, i.e.  $H_0: S_E = S_C$  against the alternative hypothesis  $H_1: S_E \neq S_C$  at a two-sided significance level of  $\alpha=5\%$ . This will be achieved by using the log-rank test stratified for the factor “patient group” as used in the randomisation procedure. The event “death from any cause” will be handled by censoring those patients at day 84 (in analogy to the approach of Cao et al, NEJM 2020). Using this approach ensures that deceased patients are considered as “not improved” over the whole observation period of 84 days. The hazard ratio for treatment group will be determined using a Cox regression model stratifying for the factor “patient group” together with a 95% confidence interval. The cumulative improvement curves are calculated using the Kaplan-Meier method together with 95% log-log-type confidence bands, and will be calculated separately for both treatment groups. In addition, cumulative improvement curves will also be calculated separately for each patient group per treatment group.

The fact that some patients from the control group might switch to the experimental group at day 10 will be ignored in the primary analysis, representing a treatment policy approach

according to the ICH E9 (R1) addendum on estimands . Patients who drop out during the trial or are lost to follow-up are taken into account as censored observations. The primary analysis will be based on the FAS according to the ITT principle.

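### Visits are timed from first plasma and restarted at crossover, but the primary endpoint runs from randomisation: day 1 is undefined for never-infused controls and can be up to 7 days late in the plasma arm

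*Protocol*

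**What the plan says.** The protocol uses more than one time origin.

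- **Visits.** Trial Schedule, footnote 1: "Timing of all visits must be based on the date of first CP administration". It makes no exception for the standard arm.
- **Start of plasma.** Section 6.6: "All patients in the experimental group have to start CP treatment within 7 days of randomization". Section 6.4 separately places day 1 no more than 7 days after baseline, and section 7.1 allows baseline up to 7 days before randomisation.
- **Crossover.** Footnote 13: "After Cross over, the visit schedule is restarted at day 1 in the experimental arm", and "The timing of subsequent visits is based on the day of first CP administration". Section 6.8 opens crossover from day 10 after randomisation and sets no latest day. Section 8 ends the study at day 84 for most patients but at "day 94 (standard arm in case of cross over), or death".
- **Endpoint.** Section 10.2.1: "Time from randomisation to clinical improvement within 84 days by two points on a seven point ordinal scale or live discharge from the hospital". Under section 10.5.4, death "will be handled by censoring those patients at day 84".
- **Scale scoring.** Section 7.3.1 starts the ordinal scale at inclusion, has it scored daily to day 28, weekly to day 56, then on days 70 and 84, and ties its end to 84 days after randomisation. It does not say which date is day 1. Table 1 shows no visit between screening/baseline and day 1.

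**The concern.** In an open-label trial whose endpoint depends partly on a scheduled score, both arms should be assessed on the same grid from the same origin. Followed literally, footnote 1 prevents this in three ways.

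- Controls who are never infused have no anchor date, so sites must invent one.
- In a plasma patient infused late, the daily grid starts up to 7 days after randomisation, runs to about day 35 instead of day 28, and puts the last visit near day 91.
- A control who crosses over goes back to a new baseline and a new daily grid, although the treatment-policy estimand needs the original baseline and clock to continue.

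What is at stake is when an in-hospital improvement is detected in each arm, and what a study-day label means in the section 10.5.5 mixed models for viral load and antibodies, where time is the repeated factor.

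**Working it through.** **The plan's own figures.** With HR 1.6, two-sided 5%, 80% power and 1:1 allocation (section 10.3), Schoenfeld gives 4 × (1.960 + 0.842)² / (ln 1.6)² = 142.1 events. The hazards are ln 2/16 = 0.0433 (control) and 1.6 × 0.0433 = 0.0693 (plasma). The 38-day event probabilities are then 0.807 and 0.928, so n = 142.1/0.868 = 163.8, or 164. Dividing by 0.95 gives 172.6, so 173, or 174 with equal arms. All stated figures reproduce, and re-anchoring visits does not change them.

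**Calendar offsets.**
- Plasma arm, lag 0 to 7 days: daily scoring ends at up to 28 + 7 = day 35 after randomisation, and the last visit falls at up to 84 + 7 = about day 91.
- Crossover at day 10: 10 + 84 = 94, which matches section 8. Crossover at day 30, for example: 30 + 84 = 114, which does not.

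**Upper bounds on patients affected, at the control hazard.**
- Improved by day 7: 1 − exp(−0.0433 × 7) = 26%.
- Improved between days 28 and 35: exp(−0.0433 × 28) − exp(−0.0433 × 35) = 7.8%.

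These count every improvement. Section 7.3.1 says all patients enter in category 4 or 5. From category 4, two points means category 2, which is discharge and has an exact date. Only in-hospital changes such as 5 to 3 depend on the grid, and the protocol does not give the share entering in category 5.

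**Effect on the log-rank test.** Simulation with 82 patients per arm, exponential times, 38 days of follow-up, an unstratified test and 4,000 runs per scenario. The lag distribution is an assumption, because the protocol gives only the maximum. In the lag rows, time is counted from randomisation and any pre-infusion improvement in the plasma arm is first recorded at day 1.

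| Scenario | Type I error | Power at HR 1.6 |
|---|---|---|
| No lag | 5.4% | 79.6% |
| Lag uniform 0–2 days | 4.8% | 80.8% |
| Lag uniform 0–7 days | 5.5% | 74.3% |

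The Monte Carlo standard error is about √(0.8 × 0.2/4000) = 0.6 percentage points for power, so the 0–2 day result cannot be told apart from no lag.

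**End of follow-up.** Under the same model, 2.6% of controls are event-free at day 84 and 1.7% at day 94. At most 0.9% of controls would have an event in that interval. The protocol itself expects the control curve to flatten at about day 38.

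**The case against.** The strongest reply is that the estimand, objectives and analysis all count from randomisation, that discharge and death carry calendar dates, and that section 7.3.1 already has the scale scored daily from inclusion. On that view footnote 1 is loose wording with little consequence. Much of this stands, and it rules out several stronger readings that a reader might infer.

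- *Late-infused patients go unscored for a week.* This follows from footnote 1 and Table 1 alone. Section 7.3.1 points the other way, so the defect is a conflict between sections, not an established gap.
- *The arms have two stated clocks.* They do not. The control clock is simply undefined.
- *The false-positive rate is inflated.* If plasma-arm times were read from plasma-based study days while control times ran from randomisation, the same simulation gives about 16% type I error with a 0–7 day lag (6% with 0–2 days), almost all favouring plasma for the longer lag. Section 10.2.1 fixes randomisation as the origin, so the plan does not call for that calculation.
- *Viral clearance during the lag favours plasma.* Nominal days are misaligned, but no direction of bias is established. Section 10.5.5 adjusts for baseline value, and a pre-infusion day-1 sample is required.
- *The first-plasma limits in sections 6.4 and 6.6 contradict each other.* Both can hold. A full 7-day lag then requires baseline and randomisation on the same day.

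Day 94 also fits the single crossover assessment that Table 1 shows at day 10. What the reply does not answer is that footnote 1 is mandatory and unqualified, leaves never-infused controls without a day 1, and conflicts with section 7.3.1. A SAP cannot recover scale scores that sites did not take.

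**Conclusion.** The schedule is wrong as written and should be corrected. The anchor for all visits does not exist for controls who never cross over, may lie up to 7 days after the endpoint's origin in the plasma arm, and is reset at crossover.

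The damage to the primary analysis is bounded. With times counted from randomisation, type I error stays near 5%. The cost is power: about 74% against 80% for a lag uniform on 0 to 7 days with early improvement first recorded at day 1, and negligible for 0 to 2 days. That result assumes exponential times, an unstratified test and delayed recording of every early improvement. Because dated discharges are not delayed, it is a worst case for that lag distribution. The 26% and 7.8% are upper bounds for the same reason. Ending at day 84 or at days 91 to 94 hardly matters for this endpoint. For viral load and antibodies, the same nominal day means different times since randomisation, with no direction of bias shown.

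**What to change.** - Define day 1 for the ordinal scale, phone follow-up and day-84 status as the randomisation date in both arms.
- Score the scale daily from randomisation, including any days before infusion.
- After crossover, keep that clock and the original baseline running. Add infusion-anchored safety visits and samples on top, without restarting the efficacy schedule.
- Analyse viral load and antibodies by actual days since randomisation. Sampling may stay tied to infusion.
- Reconcile footnotes 1 and 13, section 7.3.1 and section 8. Day 94 fits only a crossover at about day 10, while section 6.8 allows crossover from day 10 onward.
- Clarify how the first-plasma limits in sections 6.4 and 6.6 fit together, given the baseline window in section 7.1.

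The cost is an amendment to the footnotes and these sections, new eCRF visit labels and a few extra scale recordings before infusion and after crossover. The sample size does not change.

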## Abbreviations

|          |                                                 |
|----------|-------------------------------------------------|
| ADE      | Antibody Dependent Enhancement                  |
| AE       | Adverse Event                                   |
| ALT      | Alanine Amino Transferase, also known as SGPT   |
| AMG      | Deutsches Arzneimittelgesetz (German Drug Law)  |
| AP       | Alkaline Phosphatase                            |
| ARDS     | Acute Respiratory Distress Syndrome             |
| AST      | Aspartate Amino Transferase, also known as SGOT |
| ATIII    | Antithrombin III                                |
| BUN      | Blood Urea Nitrogen                             |
| CK       | Creatine Kinase                                 |
| CMV      | Cytomegalovirus                                 |
| COVID-19 | Coronavirus Disease 2019                        |
| CP       | Convalescent plasma                             |
| CRF      | Case Report Form                                |
| CRP      | C-Reactive Protein                              |
| CTC      | Common Toxicity Criteria                        |
| CTCAE    | Common Toxicity Criteria for Adverse Events     |
| DMC      | Data Monitoring Committee                       |
| DSUR     | Development Safety Update Report                |
| EC       | Ethics Committee                                |
| ECHO     | Echocardiogram                                  |
| ECMO     | Extracoporal Membrane Oxygenation               |
| ELISA    | Enzyme-linked Immunosorbent Assay               |
| EMA      | European Medicines Agency                       |
| EOS      | End of Study                                    |
| EOT      | End of Treatment                                |
| FAP      | Full Analysis Population                        |
| FiO2     | Fraction of Inspired Oxygen                     |
| FPFV     | First Patient First Visit                       |
| FSH      | Follicle Stimulating hormone                    |
| GCP      | Good Clinical Practice                          |
| GDPR     | General Data Protection Regulation              |

|                  |                                                                                                                                   |
|------------------|-----------------------------------------------------------------------------------------------------------------------------------|
| gGT              | Gamma-glutamyl transferase                                                                                                        |
| H1N1             | Hemagglutinin Type 1 and Neuraminidase Type 1 (Swine Flu)                                                                         |
| H5N1             | Hemagglutinin Type 5 and Neuraminidase Type 1 (Avian Influenza)                                                                   |
| HAV              | Hepatitis A Virus                                                                                                                 |
| HBV              | Hepatitis B Virus                                                                                                                 |
| HCV              | Hepatitis C Virus                                                                                                                 |
| HIV              | Human Immune-deficiency Virus.                                                                                                    |
| HR               | Hazard Ratio                                                                                                                      |
| IC               | Informed Consent                                                                                                                  |
| ICH              | International Council on Harmonization of Technical Requirements for
Registration of Pharmaceuticals for Human Use             |
| ICTRP            | International Clinical Trials Registry Platform                                                                                   |
| ICTRP            | International Clinical Trials Registry Platform                                                                                   |
| Ig               | Immunoglobulin                                                                                                                    |
| IKTZ             | Institut für Klinische Transfusionsmedizin und Zelltherapie (Institute for
Clinical Transfusion Medicine and Cellular Therapy) |
| IL-6             | Interleukin-6                                                                                                                     |
| IMP              | Investigational Medicinal Product                                                                                                 |
| IMPD             | Investigational Medicinal Product Dossier                                                                                         |
| IPCW             | Inverse Probability Censoring Weighting                                                                                           |
| ISF              | Investigator Site File                                                                                                            |
| ITT              | Intention-To-Treat                                                                                                                |
| LDH              | Lactate Dehydrogenase                                                                                                             |
| LH               | Luteinizing hormone                                                                                                               |
| LKP              | Leiter der Klinischen Prüfung (Coordinating Investigator according to AMG)                                                        |
| LPFV             | Last Patient First Visit                                                                                                          |
| LPLV             | Last Patient Last Visit                                                                                                           |
| MERS             | Middle East Respiratory Syndrome                                                                                                  |
| NCT              | National Center for Tumor Diseases                                                                                                |
| PaO 2 | Partial Pressure of Oxygen                                                                                                        |
| PCR              | Polymerase Chain Reaction                                                                                                         |
| pH               | Potential Hydrogen                                                                                                                |
| PLT              | Platelet                                                                                                                          |
| PRO              | Patient Reported Outcome                                                                                                          |
| PTT              | Partial Thromboplastin Time                                                                                                       |
| RBC              | Red Blood Cell                                                                                                                    |

|                  |                                                            |
|------------------|------------------------------------------------------------|
| RPSFT            | Rank Preserving Structural Failure Time                    |
| SAE              | Serious Adverse Event                                      |
| SaO 2 | Oxygen saturation                                          |
| SAP              | Statistical Analysis Plan                                  |
| SARS-CoV         | Severe Acute Respiratory Syndrome Coronavirus 2            |
| SDV              | Source Data Verification                                   |
| SGOT             | Serum Glutamic-Oxaloacetic Transaminase, also known as AST |
| SGPT             | Serum Glutamic-Pyruvate Transaminase, also known as ALT    |
| SOFA             | Sequential Organ Failure Assessment                        |
| SOP              | Standard Operating Procedures                              |
| SUSAR            | Suspected Serious Unexpected Adverse Reaction              |
| TACO             | Transfusion Associated Circulatory Overload                |
| TMF              | Trial Master File                                          |
| TRALI            | Transfusion Associated Lung Injury                         |
| WBC              | White Blood Cell                                           |
| WHO              | World Health Organization                                  |

